## Abstract

**Background:**

Long-term sick leave has considerably negative impact on the individual and society. Hence, the need to identify effective occupational rehabilitation programs is pressing. In Norway, group based occupational rehabilitation programs merging patients with different diagnoses have existed for many years, but no rigorous evaluation has been performed. The described randomized controlled trial aims primarily to compare two structured multicomponent inpatient rehabilitation programs, differing in length and content, with a comparative cognitive intervention. Secondarily the two inpatient programs will be compared with each other, and with a usual care reference group.

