### Objectives

In line with current recommendations
[24,25], the objective of this protocol article is to describe the design of a randomized controlled trial, including health economics evaluation and qualitative implementation studies alongside the trial. The design with randomization at two levels makes several comparisons possible (Figure 
1). This study will investigate the effects of short- and long-term inpatient multicomponent rehabilitation programs compared to a single-component intervention and an ‘untouched’ usual care reference group from sick-leave registers. The latter will serve as a reference group to the three interventional groups. The principal objectives are to explore the following research questions:

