### Outcomes

#### Primary outcome

Total number of sickness absence days during the 6 months after enrolment in the study (i.e. after pre-screening), obtained by national registers.

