### Randomization

Sick-listed persons will be randomized twice (see Figure 
1). Firstly, subjects sick listed in the Social Security System will randomly receive one of two invitations (Long or Short program study) to participate in the study. Those allocated to not receive an invitation will serve as an unaware control group, and their future sick leave monitored. Secondly, invited subjects who provide informed consent and are found eligible, will be randomized to the control arm (single-component ACT-program) or to the already allocated Long or Short multicomponent rehabilitation program (depending on the outcome of randomization 1). Hence there are two separate randomized controlled studies at this level (Long vs. ACT and Short vs. ACT). Both randomizations are blinded. The first randomization will be performed by a project co-worker; and the second randomization by the Unit of Applied Clinical Research (third-party) at the Norwegian University of Science and Technology (NTNU). With anonymous aggregated data, we can also compare the reference group with those who 1) do not reply to the invitation, 2) decline participation and 3) are excluded after the pre-examination.

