### Ethical considerations

REC Central - the Regional Committee for Medical and Health Research Ethics in Central Norway has approved these studies (No.: 2012/1241), and the trial is registered in clinicaltrials.gov (No.: NCT01926574). All participants enrolled in the study will take part in one of three rehabilitation programs in the specialist health care at St. Olav’s University Hospital. Those randomized to not being invited receive usual care, and the researchers will only be given anonymous aggregated information on outcome, sick-leave and sustainable RTW.

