### Strengths

This trial will be the first to investigate whether a group based rehabilitation program for patients with musculoskeletal, mental or unspecific problems can facilitate work participation, whereas comparable studies have employed rehabilitation programs tailored for populations with a specific disorder (e.g. low back pain). Employing a national register for sickness absence data eliminates recall bias and provides data from non-responders. Furthermore, our design with randomization at two levels will make it possible to assess the effects of all interventions, and also determine the effect of contacting potential participants. Sending an invitation letter instead of recruiting from e.g. general practitioners will ensure that the group is not biased by referral, improving generalizability of the results. Moreover, the RCT will be followed by economic evaluations. Finally, the qualitative studies aim to explore the implementation of the rehabilitation programs more in depth. They will shed light on barriers and facilitators for implementation of such programs by studying the participants’ and providers’ perceptions before taking part in the intervention. A realistic evaluation approach would help to describe what providers and participants perceive as the important, helpful, or difficult aspects of an inpatient multicomponent rehabilitation program.

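### The stated comparisons with the uninvited register group are not protected by the first randomisation, so they do not deliver the claimed effects of the programmes against usual care or of contact

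*Protocol article*

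**What the plan says.** Under Randomization, register-listed persons "will randomly receive one of two invitations (Long or Short program study) to participate in the study", or none. Of the last group the section says: "Those allocated to not receive an invitation will serve as an unaware control group, and their future sick leave monitored". Only invited persons who consent and are found eligible go on to the second randomisation, between ACT and the programme named in their invitation. Recruitment procedure describes the steps between: a reply, a short questionnaire screen, and an outpatient assessment by a physician, a psychologist and a physiotherapist.

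Three uses of the uninvited group are stated:

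- The abstract sets a secondary aim: "Secondarily the two inpatient programs will be compared with each other, and with a usual care reference group". Objectives says of the uninvited group: "The latter will serve as a reference group to the three interventional groups".
- Randomization adds that "we can also compare the reference group with those who 1) do not reply to the invitation, 2) decline participation", and, as a third group, persons excluded at the pre-examination.
- Strengths says the two-level randomisation "will make it possible to assess the effects of all interventions, and also determine the effect of contacting potential participants".

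Two further statements bear on these uses. The primary outcome is "Total number of sickness absence days during the 6 months after enrolment in the study (i.e. after pre-screening"). For the uninvited, Ethical considerations says "the researchers will only be given anonymous aggregated information on outcome, sick-leave and sustainable RTW".

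The article nowhere states a comparison of all invited with all uninvited persons, or any allowance for selection between the two randomisations.

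**The concern.** A randomised comparison holds between the groups as allocated. At the first randomisation these are Long invitation, Short invitation and no invitation. Enrolled participants, non-repliers, decliners and excluded persons are all subsets of the invited, defined by events after that allocation. The uninvited group contains the counterparts of all of them, and nobody can tell which is which. Setting any one subset against the whole uninvited group therefore compares different kinds of people.

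Two features add to this. Enrolment, where the primary outcome clock starts, is a date the uninvited do not have. And because the researchers receive only aggregates on the uninvited, they cannot adjust for individual characteristics.

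At stake is how the usual-care and contact results will be read. Strengths attributes them to randomisation, and Impact of results addresses the trial to policy makers. A difference produced by who replies and who passes screening could be reported as an effect of a programme or of an invitation letter.

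**Working it through.** **The plan's own figure.** Sample size gives 60 days (SD 40) against 90 days (SD 60), P = 0.05 and 90% power. Taking the test as two-sided, the mean variance is (40² + 60²)/2 = 2,600, and n = 2 × 2,600 × (1.960 + 1.282)² / 30² = 60.7, so 61 per group, as stated. Allowing for 20% loss, 61/0.8 gives 77, within the planned 80. This figure concerns programme against ACT. No sample size is given for any comparison with the uninvited.

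**Selection bias with no effect of programme or contact.** Let e be the share of invited persons who enrol. Let d be the mean sick-leave days, under usual care, of persons who would enrol minus those of persons who would not. By the first randomisation the uninvited hold the same mix, so with mean m in would-be non-enrollees the uninvited mean is m + e·d. Then:

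- enrolled minus all uninvited = (m + d) − (m + e·d) = (1 − e)·d
- non-enrolled minus all uninvited = m − (m + e·d) = −e·d
- all invited minus all uninvited = e(1 − e)·d − (1 − e)·e·d = 0

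The second line pools non-repliers, decliners and excluded persons; each taken alone would carry its own bias.

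Neither e nor d is in the documents. The table assumes e = 5–30% and d = 15 or 30 days; a negative d reverses the signs. The last two columns give the chance of a significant result (two-sided 5%) for enrolled against uninvited when there is no effect, with 80 enrolled, an assumed 1,000 uninvited and SD 60, so SE = 60 × √(1/80 + 1/1,000) = 6.97 days.

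| e | Enrolled − uninvited, d = 15 | same, d = 30 | Non-enrolled − uninvited, d = 15 | same, d = 30 | False positives, d = 15 | same, d = 30 |
|---|---|---|---|---|---|---|
| 5% | 14.25 | 28.5 | −0.75 | −1.5 | 53% | 98% |
| 10% | 13.5 | 27.0 | −1.5 | −3.0 | 49% | 97% |
| 20% | 12.0 | 24.0 | −3.0 | −6.0 | 41% | 93% |
| 30% | 10.5 | 21.0 | −4.5 | −9.0 | 33% | 85% |

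**What the protected contrast can show.** If every enrolled person gained 30 days, the difference between all invited and all uninvited would be 30·e. The number per group at 90% power, two-sided 0.05 and SD 60 is 2 × 60² × (1.960 + 1.282)² / (30e)²:

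| e | Diluted difference (days) | n per group |
|---|---|---|
| 5% | 1.5 | 33,624 |
| 10% | 3 | 8,406 |
| 20% | 6 | 2,102 |
| 30% | 9 | 934 |

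**The case against.** The strongest reply is that Strengths speaks of what the design makes possible, and the design does support a valid contrast. Non-repliers, decliners, excluded persons and enrollees together make up all the invited, so the data for invited against uninvited would exist. The wording under Randomization is permissive, and the uninvited are called a reference. The listed principal research questions contain no usual-care comparison. All of this stands, and it limits the point to the stated contrasts and the claim attached to them. It does not remove the point: the abstract plans the programme comparison as an aim, Strengths speaks of effects, and the one contrast that would justify that wording is not stated.

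A reader might infer more than the documents support:

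- *That the design cannot give an effect of contact at all.* It can estimate the effect of being invited, through the groups as allocated.
- *That the named tests cannot be run on aggregate reference data.* Statistical analyses does not assign the Mann-Whitney test or Kaplan-Meier analysis to this comparison, and both can be computed from a sufficiently detailed frequency or life table.
- *That the bias from early return to work can be sized from the 40% return-to-work share under Sample size.* That is a planning figure for one arm of a trial comparison, not a usual-care rate. Nor does the article say that sick-leave status is rechecked at the clinical assessment. Such a bias would give enrollees more days and so work against the programmes, whereas selection of motivated persons could work the other way. The net direction is unknown.
- *That the shared index date is an omission in itself.* A condensed article may leave it to the full protocol. It matters here only because the one clock the article defines cannot apply to the uninvited.

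**Conclusion.** The point holds for the comparisons with the uninvited group and for the sentence in Strengths. As stated, those contrasts are observational, and the claim that two-level randomisation yields the effects of all interventions and of contact is not delivered by them. The bias could approach the planned 30-day effect, but its size and direction rest on assumed uptake and prognosis differences, so the tabulated range illustrates and does not predict.

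It might be inferred that the trial's main result is compromised. It is not: Long against ACT and Short against ACT rest on the second randomisation, among persons already enrolled, and neither they nor the sample size depend on the uninvited group. This should be fixed, as a matter of specification and wording for a secondary comparison.

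**What to change.** 1. Define the randomised usual-care comparison as all persons allocated to a Long (or Short) invitation, whatever their response, against all persons allocated to none. Count sick-leave days in every group from the date of the NAV extraction and first randomisation.
2. Request register aggregates by allocated group: number, mean, SD and a frequency table of days.
3. Label the comparisons of enrolled persons, non-repliers, decliners and excluded persons with the uninvited group as descriptive.
4. Reword Strengths, so that the randomised contrast is said to estimate the effect of the invitation policy: contact plus whatever Long/ACT or Short/ACT mix was received.
5. If a complier-average estimate is wanted (the difference divided by uptake), make it secondary. State that it assumes an invitation has no effect on those who do not enrol, which the main Background section itself questions by treating any contact as a possible intervention. State also that it describes a mix of programme and ACT, not the programme alone.

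The cost is wording and a specification for the register request, with no additional enrolment. The drawback is imprecision: at an assumed 10% uptake a 30-day effect becomes 3 days and would need about 8,400 persons per group for 90% power. That is a reason to claim less for this comparison, not to rely on a biased one.

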**Methods/design:**

The study is designed as a randomized controlled trial with parallel groups. The Social Security Office performs monthly extractions of sick listed individuals aged 18–60 years, on sick leave 2–12 months, with sick leave status 50% - 100% due to musculoskeletal, mental or unspecific disorders. Sick-listed persons are randomized twice: 1) to receive one of two invitations to participate in the study or not receive an invitation, where the latter “untouched” control group will be monitored for future sick leave in the National Social Security Register, and 2) after inclusion, to a Long or Short inpatient multicomponent rehabilitation program (depending on which invitation was sent) or an outpatient cognitive behavioral therapy group comparative program. The Long program consists of 3 ½ weeks with full rehabilitation days. The Short program consists of 4 + 4 full days, separated by two weeks, in which a workplace visit will be performed if desirable. Three areas of rehabilitation are targeted: mental training, physical training and work-related problem solving. The primary outcome is number of sick leave days. Secondary outcomes include time until full sustainable return to work, health related quality of life, health related behavior, functional status, somatic and mental health, and perceptions of work. In addition, health economic evaluation will be performed, and the implementation of the interventions, expectations and experiences of users and service providers will be investigated with different qualitative methods.

**Trial registration:**

ClinicalTrials.gov:
NCT01926574.

## Background

Long-term sickness absence has considerable impact on social functioning, on the families of the sick-listed, the companies they work for, and society as a whole
[1]. Therefore, measures to reduce likelihood of dropping out from work have been implemented through legislation, Health, Safety and Environment acts and by different treatment and rehabilitation services. Throughout many European countries various outpatient and inpatient rehabilitation programmes have been established to prevent long-term sickness absence and permanent work disability. However, the documented effects of work rehabilitation on working capacity, work participation and health are sparse
[2].

Most work rehabilitation programs described in the scientific literature are designed for single or a specific diagnostic group. Several studies have investigated return-to-work (RTW) interventions for musculoskeletal disorders
[3], particularly for workers with non-specific low back pain
[4-7]. Far fewer studies are conducted for workers with mental problems, although RTW programs have been investigated in absenteeism due to mental disorders
[8], distress
[9], adjustment disorders
[10] and depression
[11]. It is now recognized that many patients on sick leave have more than one health complaint. As an example, previous studies of workers on sick leave due to chronic low back pain in Norway showed that less than 2% reported low back pain as their only complaint
[12]. In addition, a recent study on sick listed patients with low back pain showed that one out of three had psychiatric comorbidity
[13]. Similar findings are reported from other western countries
[14,15], demonstrating a substantial overlap of musculoskeletal, mental, and other disorders.

The overlap and complexity of health complaints makes it difficult for general practitioners to agree on the diagnosis of patients with several health complaints, and the diagnosis given to patients with similar symptoms may vary greatly between general practitioners
[16]. Since there is considerable degree of comorbidity among these patients, the present trial will employ a comprehensive rehabilitation model suited for patients with musculoskeletal disorders as well as common mental disorders and/or unspecific disorders. This is in line with the paradigm shift of occupational medicine from disease treatment to disability rehabilitation and management
[17,18].

In Norway, tertiary institutional care occupational rehabilitation programs have been active for more than 27 years. Although some evaluations have been performed
[19,20] none have used a randomized research design. Thus, the effects on work participation and health outcomes of institutional occupational rehabilitation programs are largely unknown. Further, institutional occupational rehabilitation programs in Norway usually last ~ four weeks, and the patients stay at the center during this period. However, the rationale for a four-week rehabilitation period with full rehabilitation days is based on experience and convenience rather than scientific evidence. Hence, rehabilitation programs with different durations should be investigated. In addition, physical activity/exercise and coping of health complaints are emphasized in several of these programs, whereas there is generally little work place involvement
[21]. Conversely, RTW-programs described in the scientific literature have suggested that structured meetings between employee, employer and occupational health professionals are important for improving RTW rates
[22,23].

The primary purpose of this study is to explore the effect of two different multicomponent work-rehabilitation programs on sickness absence, motivation for work, somatic- and mental health, and related outcomes. The *Long* program consists of 3 ½ weeks with full rehabilitation “work” days. The *Short* program consists of 4 + 4 full days of rehabilitation, separated by two weeks. In the Short program a workplace visit will be performed, in addition to the 4 + 4 rehabilitation days, if considered relevant by the worker and the rehabilitation team. A single-component psychological intervention will serve as a comparative control arm. Using a design where participants will be randomized twice, both the Long and Short program will be compared with the comparative control arm in separate randomized controlled studies, but in addition we will also compare the Long with the Short program. Furthermore, as any form of contact can be perceived as an intervention, an ‘untouched’ control group will also be followed in national registers and used as a usual care reference.

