**Figure 1 F1:**
[figure not shown]
**Design of the study.** ACT: Comparative outpatient Acceptance and Commitment Therapy Rehabilitation group.

• Are the multicomponent rehabilitation programs more effective in reducing sickness absence compared to the single component Acceptance and Commitment Therapy (ACT) program (i.e. Short vs. ACT; Long vs. ACT), and are there differences between the Long and Short programs?

• Are the multicomponent rehabilitation programs cost effective compared to the single component ACT program (i.e. Short vs. ACT; Long vs. ACT)?

• Are the patients’ and service providers’ expectations before participation in the multicomponent rehabilitation programs, in accordance with their experiences afterwards?

• According to the patients’ and service providers’ experiences; have the multicomponent rehabilitation program been implemented as planned?

• Are the multicomponent programs more effective in improving secondary outcomes (e.g. mental or physical health, or motivation for return to work) than the single component Acceptance and Commitment Therapy (ACT) program?

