### Recruitment procedure

NAV provide monthly lists of persons meeting the inclusion criteria. The assigned project co-worker checks eligibility performs the first randomization (Figure 
1) and sends out invitations to potential participants. They receive available information of the project through written leaflets, website of the rehabilitation centre and are invited to call a project co-worker if they have queries. The potential participants are asked to answer a two-page questionnaire and a consent form indicating whether they agree or disagree to take part in the study, or if they require more information. Contacted persons are asked to reply to the project co-worker using an enclosed prepaid envelope. Positive answers are forwarded to the researchers who determine initial eligibility based on the short questionnaire. Prior to enrolment in the study a physician, psychologist and physiotherapist will perform an outpatient assessment of eligibility. Results from the outpatient assessment will be provided to the relevant health personnel and utilized in the rehabilitation program.

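### Among enrolled participants, Long v Short is not a randomised comparison: the programme is fixed by the invitation, before consent and eligibility assessment, and the article does not say so

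*Protocol article*

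**What the plan says.** **The comparison.** The Background describes Long v ACT and Short v ACT as separate randomised studies and continues: "but in addition we will also compare the Long with the Short program". The first research question under the principal objectives asks "are there differences between the Long and Short programs". The Abstract gives the same comparison a secondary rank.

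**The sequence.** Under Randomization, "subjects sick listed in the Social Security System will randomly receive one of two invitations (Long or Short program study) to participate in the study"; a further group is not invited. Under Recruitment procedure, invitees receive information and return "a consent form indicating whether they agree or disagree to take part in the study, or if they require more information". A physician, a psychologist and a physiotherapist then assess eligibility before enrolment. Only then does the second randomisation take place: "invited subjects who provide informed consent and are found eligible, will be randomized to the control arm" or to the "already allocated Long or Short multicomponent rehabilitation program (depending on the outcome of randomization 1".

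**What is called randomised.** The Randomization section draws the conclusion itself: "Hence there are two separate randomized controlled studies at this level (Long vs. ACT and Short vs. ACT".

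**What is not said.** The Objectives credit the two-level randomisation with allowing several comparisons. The Limitations section covers blinding and generalisability but not self-selection. Statistical analyses gives a Mann-Whitney test for sick-leave days and nothing specific to Long v Short.

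**The concern.** A comparison keeps the protection of randomisation only if nothing that depends on the allocation decides who is analysed. Here two filters, acceptance and clinical eligibility, act after Long or Short has been allocated and before anyone enters the trial.

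The two offers differ in ways that could affect acceptance. One is about 3.5 weeks at a residential centre. The other is two four-day stays with two weeks at home between them and a possible workplace visit. If people with different family, job or health circumstances accept each offer, the enrolled Long and Short groups can differ in prognosis before treatment starts. A direct comparison would then report part of that difference as an effect of programme length, a question for which the Background says evidence is lacking.

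**Working it through.** **1. Who is compared, and when they were randomised**

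| Contrast | Randomised when | Filters between randomisation and analysis |
|---|---|---|
| Long v ACT, among those invited to Long | Second randomisation | None at entry |
| Short v ACT, among those invited to Short | Second randomisation | None at entry |
| Enrolled Long v enrolled Short | First randomisation | Reply, consent, eligibility assessment |
| Everyone invited to Long v everyone invited to Short | First randomisation | None |

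Only the third row has lost the protection of randomisation.

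**2. The plan's own figure**

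Inputs from Sample size: means of 60 and 90 days, SDs of 40 and 60, alpha 0.05 (two-sided assumed), power 90%.

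n per group = (40² + 60²) × (1.960 + 1.282)² / 30² = 60.7, rounded up to 61. This agrees with the stated 61. Allowing for 20% loss, 61 / 0.8 = 76.25, so 77, which the planned 80 covers. None of these figures is disputed.

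**3. Precision of the possible Long v Short contrasts**

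These use SD 40 in the programmes, SD 60 in ACT and 80 per programme arm.

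- Direct: SE = √(2 × 1600/80) = √40 = 6.3 days; 95% CI ± 12.4.
- One programme v ACT: SE = √(1600/80 + 3600/80) = √65 = 8.06 days.
- Anchored, (Long − ACT) − (Short − ACT), with 80 ACT participants in each stream: SE = √(2 × 65) = √130 = 11.4 days; 95% CI ± 22.3.
- Anchored, with one ACT arm of 80 split 40/40: SE = √(2 × 1600/80 + 2 × 3600/40) = √220 = 14.8 days; 95% CI ± 29.1.

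The last case is shown because the Design section speaks of three parallel groups and Sample size of 80 in each arm. That leaves open whether ACT has 80 people in total or 80 per stream.

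**4. What a selection shift would do to the direct test**

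The documents give no uptake or prognosis data, so the shift b is an assumption. With no true difference, the two-sided false-positive rate is Φ(−1.96 + b/SE) + Φ(−1.96 − b/SE).

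| Assumed shift b (days) | 0 | 5 | 10 | 15 |
|---|---|---|---|---|
| SD √((40² + 60²)/2) = 50.99 in both arms, SE 50.99 × √(2/80) = 8.06 | 5% | 10% | 24% | 46% |
| SD 40 in both arms, SE 6.32 | 5% | 12% | 35% | 66% |

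The first row is the more cautious and is the one quoted in the conclusion.

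A simulation checked it with the planned Mann-Whitney test: 2000 runs, 80 per arm, SD 50.99, and consent depending on prognosis in opposite directions for the two invitations. At mean shifts of about 0, 5, 10 and 16 days, direct Long v Short rejected in 4, 10, 24 and 48% of runs. Long v ACT and the anchored contrast both stayed at about 5%.

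**The case against.** Several points on the other side have force.

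- **The article does not call enrolled Long v Short randomised.** The Background sets it apart from the two randomised studies, and the Randomization section names only those two. This stands. The fault is narrower: the Objectives attribute the comparisons to the two-level randomisation, and the Limitations omit the selection. A separate analysis plan may deal with adjustment, but it would not change what the article tells its readers.
- **The comparison may be only secondary.** The Abstract says so, while the Objectives place it under the principal questions. The documents do not settle the rank, and a secondary comparison still needs the right label.
- **The invitation letters are not shown.** That they disclose the programme is a strong inference from two separately named invitations and informed consent. The statement that both randomisations are blinded does not rebut it, since the invitations differ and the Limitations say participants cannot be blinded. A reader might also infer that eligibility assessors knew the invitation type; nothing in the documents supports that.
- **The anchored contrast is not a free remedy.** It removes a prognostic difference between the streams, but it assumes that programme effects do not differ between the two accepter populations. It is also much less precise. So it belongs beside the direct estimate and need not replace it.
- **The all-invited contrast answers another question.** It mixes non-participants and ACT recipients into both sides. A reader might assume the data for it are all at hand, but for non-repliers, decliners and excluded people the article provides only anonymous aggregated data.

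**Conclusion.** The point holds for enrolled Long v enrolled Short only. That contrast conditions on consent and eligibility, both of which come after the randomisation that set the programme, so it is open to selection bias. It would be wrong to infer that the trial's main contrasts are compromised: Long v ACT and Short v ACT are randomised after both filters and are unaffected. Nor do the documents show that a bias exists. They show that the design does not protect against one.

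The size is unknown. Under the assumed shifts of 0, 5, 10 and 15 days, with no true difference, SD 50.99 and 80 per arm, the direct test's false-positive rate is about 5, 10, 24 and 46%. What changes is the strength of any conclusion on programme length, which the direct contrast can support only as exploratory evidence.

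**What to change.** 1. State in the Objectives and Limitations that direct Long v Short among enrolled participants is non-randomised and exploratory. Reconcile its rank between the Abstract and the Objectives.
2. Adjust the direct contrast for baseline variables that the questionnaires already collect.
3. Report uptake and baseline characteristics by invitation type. Compare ACT participants from the Long-invited stream with those from the Short-invited stream as a check on selection.
4. Present alongside it the anchored contrast, (Long − ACT) − (Short − ACT), each difference taken within its own stream. State the assumption that programme effects do not differ between the two accepter populations, and say how many ACT participants each stream contributes.
5. Where aggregate register data (counts, means, SDs) permit, report the randomised contrast of everyone invited to Long v everyone invited to Short, labelled as an effect of invitation and not of programme length.

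**Cost.** Items 1 to 4 need wording and some programming but no new participants; item 5 depends on what the register holder can supply. The price is precision: the anchored standard error is 11.4 days, or 14.8 with a split ACT arm, against 6.3 for the direct contrast. In the split case the 95% interval of about ± 29 days is nearly as wide on each side as the 30-day planning effect.
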